### Participants

The in- and exclusion criteria of this study are presented in Table 1. Patients will be screened by a physician and a manual therapist at the MRC. Based on history, physical examination and evaluation of at least one medical image obtained in the past 12 months (X-ray, CT, MRI), serious pathology of the spine will be excluded. A high Body Mass Index (BMI) could hamper the planned sensor-based movement control intervention as a result of movement artifacts (22); therefore, patients are excluded if the BMI is higher than 35 (kg/m^2^). To avoid the risk of electromagnetic interference with the inertial sensors, patients with implanted electronic devices of any kind are excluded from this study (23).

**Table 1 T1:** In- and exclusion criteria.

**Inclusion criteria**
Between 20 and 60 years of age
Experienced low back pain on a daily basis over the last 3 months, with or without accompanying leg pain above the knee
**Exclusion criteria**
Any condition (other than chronic low back pain) that might interfere with motor control of the spine
A recent (< 5 years) surgical intervention of the spinal column or a spinal fusion.
Proven serious pathology of the spine and related structures, infections, recent fractures
Psychiatric disorders
Signs of neurological compression; loss of sensory or motor functions in the legs and/or pelvis and/or radiating pain in the lower leg and/or foot
The use of drugs that influence the reaction time
A body mass index of 35 (kg/m^2^) or more
Implanted electronic devices of any kind

### Sample size

The main objective of this study is to assess if a Group x Time interaction effect exists for movement control of the spine, i.e., if movement control of the spine changes differently between groups over the course of the intervention. To the best of our knowledge, currently no studies have been performed in which spinal movement control, as defined in the current paper, is both trained and assessed before and after training, which complicates the estimation of an expected effect size. For the study outcome to be clinically meaningful we have set the goal to detect or reject an arbitrary effect size of 0.25 (24). In other words, if the effect size would be below 0.25, we would consider this result to be too small to be of interest. Differences in movement control of the spine in low back pain patients and healthy controls in terms of tracking error of a spinal movement controlled tracking task were reported by Willigenburg et al. (12). The tracking error in healthy controls was 0.332 degrees (SD 0.103) and in low back pain patients 0.422 degrees (SD 0.634), which is a large effect size (>0.8). No data about the expected effect of a sensor-based movement control intervention on these outcomes are available. However, a recent study from Matheve et al. demonstrated that low back pain patients can alter their movement behavior using a sensor-based intervention during a single session (14). Hence, we expect that low back pain patients will be able to perform equally well on movement control tasks by the end of the intervention as healthy controls without an intervention. If the static motor control group reaches 75% of the effect of the sensor-based movement control group, corresponding to an effect size of 0.25 (considering the effect of the intervention is equally large as the standard deviation of the effect), a total sample size of 54 (27 per group) would suffice to demonstrate a Group x Time interaction effect at a power of 95%. In case of a drop-out an additional patient will be recruited (with a maximum of 10 patients).

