### Randomization, blinding and treatment allocation

This study is quasi-randomized and non-concealed. Patients will be screened in the first week of the multidisciplinary rehabilitation programme (2 weeks prior to baseline data collection). Enrolment and allocation will be 1 week prior to baseline data collection after consent of the patient. Patients will be enrolled and allocated to each intervention by one of the investigators ([name]) based on the starting date of the multidisciplinary rehabilitation programme. The research team has no influence on the starting date of each patient. If two patients start on the same date, allocation order will be alphabetically (based on the patients last name). The first five patients were allocated to the static motor control group, followed by five patients in the sensor-based movement control group and so forth until 30 patients have completed each intervention. This random allocation sequence was chosen by the investigators to keep group therapy planning feasible. Patients and therapists will not be blinded as this is practically impossible, however they will not be informed about the hypotheses of the study. The primary study outcome (spinal movement tracking error) will be calculated using a computer algorithm (custom made in D-flow, Motek, Amsterdam, The Netherlands) that will work independent of treatment allocation. Investigators involved in the statistical analysis will not be blinded to group. The clinical movement control battery tests will be recorded on video and scored by two examiners that are blinded to time (before/after intervention) and allocation.

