### Statistical analysis

To evaluate if movement control of the spine changes differently between groups over the course of the treatment, repeated measures ANOVAs will be used to evaluate if a significant Group x Time interaction effect exists for the tracking error during each tracking task separately, the average tracking error of the tracking tasks and the total score of the clinical movement control test battery. The main effects of Group and Time will also be assessed using the same ANOVA. In addition to the total score of the clinical movement control test battery by Luomajoki et al. (19, 20) the performance on the individual tests that comprise the test battery will also be reported per group at T0 and T1.

Secondary study parameters will be assessed in the same manner as described above without correction for multiple testing, because these analyses are of an exploratory nature, and we want to limit the probability of type 2 errors. For the questionnaires that will be filled out on more than two occasions, we will perform *post-hoc* independent t-tests, with LSD correction, comparing results between groups at each point in time. Patient characteristics and all questionnaires filled out during the first testing day will be compared between groups using independent sample *t*-tests without correction for multiple testing to evaluate if differences existed at baseline. Statistical analyses in this study will not be adjusted for baseline differences between groups, as recommended by de Boer et al. (32). Independent of normality, parametric statistics will be used in this study and the alpha level will be set at 0.05 (33).

Data from patients who attended less than 10 sessions are not included in the statistical analysis. In addition, the data is also not included if patients have dropped out of the study before T1.

Missing data will be handled by using complete case analysis with all repeated measures ANOVAs between T0 and T1 and independent *t*-tests between T0, T1 and T2 and between To, T1, T2 and T3.

All statistical analyses will be performed using R version 4.1.1.

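### The sample-size goal is to detect or reject an effect of 0.25, but on the scale on which the protocol words that effect, 60 patients and a test against zero can do neither

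*Protocol article*

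**What the plan says.** The protocol article, under Sample size, gives 0.25 two roles. It is the target of the design: "we have set the goal to detect or reject an arbitrary effect size of 0.25". It is also a threshold of interest: "if the effect size would be below 0.25, we would consider this result to be too small to be of interest".

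The same section puts the figure into words: "If the static motor control group reaches 75% of the effect of the sensor-based movement control group, corresponding to an effect size of 0.25", with the qualification "considering the effect of the intervention is equally large as the standard deviation of the effect". It concludes that "a total sample size of 54 (27 per group) would suffice to demonstrate a Group x Time interaction effect at a power of 95" per cent. Under Randomization, blinding and treatment allocation, recruitment runs "until 30 patients have completed each intervention".

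Under Statistical analysis, the decision on movement control is a significance test: "repeated measures ANOVAs will be used to evaluate if a significant Group x Time interaction effect exists", and "the alpha level will be set at 0.05". The article gives no rule that compares the result with 0.25.

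**The concern.** To reject an effect of a given size, the data must be shown to be incompatible with that size. A Group x Time F test has a null of zero. Failing to reach significance excludes 0.25 only if the trial had very high power at 0.25. The question is whether this trial has that power on the scale in which the protocol describes its effect.

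A null result is plausible here. Both arms train, both receive the same rehabilitation programme, and the Discussion concedes that other therapies may reduce the contrast. The Discussion also expects the results to bear on clinical decisions. If the power is not there, the stated goal invites the conclusion that sensor-based training has no advantage of interest, from data still compatible with differences well above the threshold.

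**Working it through.** **Inputs.** Completers: 30 per arm (Randomization section); 27 per arm is the stated minimum (Sample size). Alpha is 0.05, taken as two-sided because the F test is non-directional. The article gives no correlation between T0 and T1, so any value used is an assumption. With two time points, the Group x Time F test is equivalent to a two-sample t-test on change scores.

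**1. Reproducing the stated 54 at 95%.** For a 2 x 2 within-between interaction, λ = f² × N × m / (1 − ρ).
- With f = 0.25, N = 54, m = 2, ρ = 0.5: λ = 0.0625 × 54 × 2 / 0.5 = 13.5, and power is 95.0%. The figure reproduces.
- It depends on ρ. The N needed for 95% power is 106 at ρ = 0, 80 at 0.25, 54 at 0.5 and 34 at 0.7.
- In terms of change scores, λ = (n/2) × d² = 13.5 × d² with n = 27, so d = 1.0 SD of change.

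**2. The effect as worded.** If the sensor arm's effect is E and the SD of the effect is also E, the static arm gains 0.75E. The gap is 0.25E, so d = 0.25E / E = 0.25 SD of change. A gap of 1.0 SD (step 1) would mean that the static arm gains nothing, not 75%.

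**3. Can the trial detect 0.25 SD?** SE = √(2/n); noncentrality = 0.25 / SE.

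| Per arm | SE | Noncentrality | Power | Missed |
|---|---|---|---|---|
| 30 | 0.258 | 0.97 | 15.9% | 84.1% |
| 27 | 0.272 | 0.92 | 14.7% | 85.3% |

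Power of 95% at this effect would need about 417 per arm.

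**4. Can the trial reject 0.25 SD?** The 95% half-width is t(0.975, 2n − 2) × SE: 0.52 SD with 30 per arm and 0.55 SD with 27.
- An interval centred on zero still contains 0.25 SD.
- With a true difference of zero, the upper 95% limit falls below 0.25 SD in 15.7% of trials with 30 per arm and 14.5% with 27. With a one-sided 5% bound and 30 per arm it is 24.6%.
- The half-width is also the significance cut-off. An observed difference between 0.25 and 0.52 SD would count as of interest yet be non-significant.

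**5. When non-significance does reject the target.** At 95% power the target equals (1.960 + 1.645) × SE = 3.605 × SE. A non-significant estimate lies below 1.960 × SE, so its one-sided 95% upper bound lies below 3.605 × SE, which is the target. Check at 417 per arm: SE = √(2/417) = 0.0693, and 3.605 × 0.0693 = 0.25. With 30 per arm, 3.605 × 0.258 = 0.93 SD, far above 0.25 SD.

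**6. The Cohen's f reading.** With ρ = 0.5, power is 95.0% at N = 54 and 96.8% at N = 60, so 3 to 5% of trials miss. If there is no true difference, the 95% interval lies within ±1.0 SD in about 94% of trials (30 per arm) or 90% (27 per arm). Rejection is then achievable, but only of a full 1.0 SD.

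**The case against.** The strongest reply is that detecting or rejecting an effect by significance is a coherent aim at the power the protocol claims. Step 5 shows this is right in general: at a true 95% power for 0.25, a non-significant result is itself roughly a 5%-level rejection of 0.25 in the sensor arm's favour. It would be wrong to say that a test against zero could never serve, or that correcting the power would leave the problem untouched. The difficulty arises from the effect-scale and power error and should be corrected with it. What the reply does not rescue is the plan as worded, where power is about 16%.

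Three stronger readings are tempting, and the document does not support them.
- A reader might infer that p > 0.05 will be reported as rejection. The article does not say so, and its sentence on the threshold refers to the size of the effect, not to p. It gives no other rule, however, and a point estimate below 0.25 would not exclude 0.25 either.
- A reader might take the 84% miss rate as unconditional. It holds on the worded scale; on the Cohen's f reading with ρ = 0.5 it is 3 to 5%.
- A reader might fault the article for not mentioning confidence intervals. A condensed article may leave these to the full plan. The point rests on the goal and the test that the article itself fixes.

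**Conclusion.** The point holds in this limited form. On the protocol's worded scale (0.25 SD of change), the trial has about 16% power with 30 per arm (15% with 27) and a 95% interval of about ±0.52 SD. With no true difference, it would exclude 0.25 SD in only about 16% of trials. It can be expected neither to detect nor to reject its threshold, and a non-significant result should not be read as rejection. The goal is coherent only if power at 0.25 really is 95%. That reproduces with Cohen's f and an assumed correlation of 0.5, a difference four times the one the 75% scenario describes.

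The result assumes a two-sided test and that the SD in the protocol's wording is that of the change. If it is the SD of raw scores, the miss rate at N = 60 is about 84%, 77% and 67% for correlations of 0.5, 0.7 and 0.8, so the conclusion does not turn on that choice.

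**What to change.** Under Sample size, state 0.25 on one named scale and reconcile it with the 75% scenario and the claimed power. Under Statistical analysis, report the between-group difference in T0 to T1 change in average tracking error, in degrees and in SD of change, with its 95% confidence interval. State that an effect of interest is rejected only if the limit favouring the sensor arm lies below the threshold, and that any other non-significant result is inconclusive.

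If the threshold is 0.25 SD of change, delete *or reject*, restate the power (about 16% with 30 per arm), and say that 60 patients cannot be expected to exclude it. If Cohen's f is meant, state the assumed correlation, say that the target is 1.0 SD of change when that correlation is 0.5, and withdraw the 75% scenario.

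The cost is wording in two sections and one interval from data already collected, with no extra patients or measurements. On the 0.25 SD scale, the downside is that a null result will usually have to be reported as inconclusive.

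### With 54 patients the trial has about 15% power, not 95%, for the scenario behind its sample size, because a 0.25 SD difference in change appears to have been entered as Cohen's f = 0.25

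*Protocol article*

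**What the plan says.** The protocol article's Sample size section makes three linked statements.

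- The target: "we have set the goal to detect or reject an arbitrary effect size of 0.25". Anything below this is described as too small to be of interest. The metric (standardised difference d or Cohen's f) is not named.
- The scenario that produces the target: "If the static motor control group reaches 75% of the effect of the sensor-based movement control group, corresponding to an effect size of 0.25", with the scale set by "considering the effect of the intervention is equally large as the standard deviation of the effect".
- The result: "a total sample size of 54 (27 per group) would suffice to demonstrate a Group x Time interaction effect at a power of 95" per cent.

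The Statistical analysis section gives the test ("repeated measures ANOVAs will be used to evaluate if a significant Group x Time interaction effect exists for the tracking error") and the significance level ("the alpha level will be set at 0.05"). The Data collection section gives two measurements of movement control, T0 and T1. The Design section plans 30 patients per group.

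**The concern.** The scenario fixes its own metric. If the sensor group changes by one SD of the change and the static group by 75% of that, the gap is a quarter of an SD of change. This is a standardised mean difference, and a small one. A two-group trial with 27 per group cannot have 95% power for a difference of that size, so the scenario, the sample size and the power cannot all be right.

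This paragraph is the only justification of the sample size for the main objective. It also says how results will be judged, by aiming to "detect or reject an arbitrary effect size of 0.25" and treating smaller effects as uninteresting. A reader who believes the 95% would take a non-significant interaction as good evidence that the two exercise types differ by less than the threshold. In fact the trial would miss a true difference of 0.25 SD about 85% of the time.

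**Working it through.** **Inputs.** N = 54 (27 per group), power 95%, effect size 0.25 and the 75% scenario come from Sample size. Alpha 0.05 and the Group x Time test come from Statistical analysis. Two time points come from Data collection, and 30 per group from Design. The pre-post correlation ρ is not given in the article, so ρ = 0.5 below is an assumption.

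**1. Reproduce the 54.** For the interaction with 2 groups and m = 2 times, with 0.25 read as Cohen's f:

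λ = f² × N × m / (1 − ρ) = 0.0625 × 54 × 2 / 0.5 = 13.5, with df 1 and 52.

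The noncentral F gives power 0.9501. At N = 52 it is 0.942, so 54 is exactly the smallest even N.

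**2. What that input means in SDs of change.** With two time points the interaction test is the two-sample t-test on change scores, for which λ = d² × N / 4, with d in SDs of change. Setting d² × 54 / 4 = 13.5 gives d² = 1, so d = 1.00. Equivalently, d = 2f × √(2 / (1 − ρ)) = 0.5 × √4 = 1.0. If the sensor group improves by 1 SD, the static group then improves by 1 − 1 = 0, which is 0% of the effect rather than 75%.

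**3. Power for the stated scenario.** d = 1.00 − 0.75 = 0.25.

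| N | λ = 0.0625 × N / 4 | Power |
|---|---|---|
| 54 | 0.84 | 14.7% |
| 60 | 0.94 | 15.9% |
| 506 | 7.91 | 80% |
| 834 | 13.03 | 95% |

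At ρ = 0.5 this scenario corresponds to f = 0.0625, a quarter of the value that reproduces 54. A one-sided test with 54 patients would reach only 23%.

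**4. What 54 patients can detect.** 95% power at 1.00 SD of change and 80% power at 0.78 SD. These hold whatever ρ is, because the scale is the SD of the change itself.

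**5. Can 0.25 be rejected?** The half-width of the 95% confidence interval for the difference, in SDs of change, is t(0.975, N − 2) × √(4/N):

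- N = 54: 0.546.
- N = 60: 0.517.

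Even an observed difference of exactly zero would leave 0.25 SD well inside the interval.

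**6. Sensitivity to the meaning of SD.** If the SD is read as that of the outcome rather than of the change, d = 0.25 / √(2(1 − ρ)). Power with 54 patients is then:

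| ρ | 0 | 0.3 | 0.5 | 0.7 | 0.8 | 0.9 | 0.95 |
|---|---|---|---|---|---|---|---|
| Power | 9.8% | 11.9% | 14.7% | 21.4% | 29.7% | 52.2% | 81.3% |

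Reaching 95% needs d = 1, so 2(1 − ρ) = 0.0625 and ρ ≈ 0.97.

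**The case against.** The strongest reply is that the sponsor meant Cohen's f throughout. The metric is never named, and 0.25 is first introduced as an arbitrary value with a citation, before the scenario. On that reading the statement that 54 patients give 95% power for 0.25 is correct at ρ = 0.5, and the mistake is confined to the 75% sentence. That is possible, but it does not rescue the paragraph. The 75% scenario would then be wrong by a factor of four, and the threshold of interest would be a full SD of change, so a difference of 0.9 SD would count as too small to matter.

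It is also fair that the use of f is an inference from an exact numerical match. A plain two-sample comparison with d = 1.0 gives 54 as well, and the text does contain an effect equal to one SD. The sponsor may have taken that route instead. The conclusion does not depend on which: both routes power the trial for a 1.0 SD difference.

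A condensed article may leave the correlation to the full protocol, so its absence is not itself a fault. It does not affect the 14.7%. It matters only under the outcome-SD reading, where about 0.97 would be needed. The Primary outcome section says the reliability of the measure is unknown, so such a value cannot be presumed.

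Finally, the plan contains no explicit rule equating a non-significant result with an effect below 0.25. That stands: the misreading is a risk created by the wording, not a stated rule.

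**Conclusion.** The stated scenario and the stated power are incompatible. For a 0.25 SD difference in change, two-sided alpha 0.05 and equal groups, power is about 15% with 54 patients and about 16% with 60, against a claimed 95%. The trial would need 834 patients for the claim to hold. What 54 patients support is 95% power for a difference of 1.0 SD of change. The aim of rejecting 0.25 is not achievable on the SD-of-change scale, given an interval half-width of about 0.55 SD (0.52 SD with 60).

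This rests on taking the SD as that of the effect, as the text says. The alternative reading does not reach 95% at any correlation below about 0.97. The explanation that d was entered as f is an inference, but the contradiction holds whether 0.25 is d or f. It must be corrected, because it is the only basis given for the sample size.

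**What to change.** Keep the sample and restate what it provides. Suggested text: *54 patients (27 per group) give 95% power for a between-group difference in change of 1.0 SD of the change, and 80% power for 0.78 SD (two-sided alpha 0.05).* If the calculation was run with f = 0.25 and a pre-post correlation of 0.5, say so, and name the metric.

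Delete the sentence equating 0.25 with a static group that reaches 75% of the effect, and delete the aim of detecting or rejecting 0.25. If a threshold of interest is kept, define it in degrees or in SDs of change.

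Report the between-group difference in change with its 95% confidence interval as the primary result; the planned interaction test is already the test of this difference. State that a non-significant interaction will not be interpreted as showing an effect too small to matter.

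The cost is rewording the sample-size section and the way conclusions are drawn, and a less favourable power statement. No extra patients and no change of test are needed. The article reports enrolment as ongoing, so the correction can be made before the analysis.

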### Interventions

The Sensor-Based Movement Control and Static Motor Control intervention will be offered over a course of 8 weeks (weeks 2–9 of the study), each week consisting of two supervised therapy sessions of 20–30 min and four non-supervised home exercises of 5–10 min resulting in nearly one training session every day of the week for 8 weeks.

The supervised sessions are provided by five experienced (4–10 years) physio- and occupational therapists from the MRC that are trained to provide both the intended interventions. The therapists can also provide the regular therapies in the multidisciplinary rehabilitation programme of a patient. Three training moments are given to all therapists at the same time by the investigators to understand the content of the interventions and how to offer this to the patients during 8 weeks. The quality will be assured by several evaluation meetings with the investigators and investigators will check the content of the sessions by occasionally being present at the supervised sessions throughout the study. The first four sessions will be individual, i.e., one patient supervised by one therapist. In these sessions, the capacity of the patient will be determined by the therapists and the patient will get acquainted with the basics of the training. The final 12 sessions will be in groups, with a maximum of three patients in the same intervention per session, supervised by one therapist. The patients will not have the same therapist throughout the programme to keep the rehabilitation planning feasible. The therapists will monitor the progress and challenge the patient if needed during all sessions. There is a standard protocol for exercises throughout the sessions, for both the sensor-based movement control and static motor control group. This protocol was composed by two experienced physiotherapists/human movement scientists and are based on literature (6). Therapists are allowed to modify the standard exercises to match the difficulty level to the capacity of the patient. The standard exercises can also be deviated from to the need of the individual patient as long as it is within the scope of the assigned intervention. There is no standardized approach for modifications in progression, however all modifications will be registered. An example of the protocol for week four is presented in Figure 2. Attendance of the supervised sessions will be registered.

